### Participants

A total of at least 165 participants will be recruited (Multimedia Appendix 1). The target population will consist of children who exhibit symptoms and signs suggesting ADHD who contact the health system and who may or may not have the disorder. It will be attempted to represent this population through a source population consisting of (1) children aged 7-12 years who either received a prior diagnosis of ADHD (cases; predominantly hyperactive/impulsive or combined presentation or predominantly inattentive) or (2) children attending routine pediatric check-ups at the Puerta de Hierro University Hospital in Majadahonda (HUPHM) who do not meet criteria for any significant psychiatric disorder (controls). Recruitment ended in December 2024. Accordingly, our study was a convenience series of participants.

A data monitoring committee was not considered necessary due to the low-risk nature of the study; oversight is ensured through standard monitoring procedures.

### Instruments

#### Tanner Scale

The Tanner sexual maturity scale will be administered to assess the degree of development and physiological status in participants [60].

#### Strengths and Difficulties Questionnaire

The Strengths and Difficulties Questionnaire (SDQ) is a brief screening questionnaire that helps detect pediatric psychopathology in individuals between 4 and 16 years old, with measures of social, emotional, and behavioral functioning. It consists of 5 scales (emotional symptoms, conduct problems, hyperactivity/inattention, peer relationship problems, and prosocial behavior) and provides a total score of difficulties. Due to its use in scientific literature and the demonstration of its good psychometric properties, this scale has been used to rule out relevant psychiatric pathology that could interfere with the study [61,62].

#### Child and Adolescent Behavior Inventory

The Child and Adolescent Behavior Inventory (CABI) consists of 9 subscales that allow measuring symptoms of inattention, hyperactivity, SCT, anxiety, depression, oppositional defiant disorder, prosocial attitude, and academic and social difficulties. The parent version will be used for this study. Each scale is made up of several items, and it must be specified whether the absence or presence of such symptoms has an impact on an academic or social level (no difficulty, mild difficulty, moderate difficulty, or severe difficulty). We will use the most recent normative data that have been published for Spanish youth aged 5‐16 years [63].

#### ADHD Rating Scale IV

The validated Spanish version of the Attention Deficit/Hyperactivity Disorder Rating Scale IV (ADHD-RS-IV) will be used to check the severity of ADHD, considering the total score of the scale—composed of 18 items that are scored according to a 4-point Likert scale (0=never or rarely, 1=sometimes, 2=often, or 3=very often)—and the scores of the 2 subscales of the test, inattention and hyperactivity/impulsivity [64].

#### Wechsler Intelligence Scale for Children, Fifth Edition

The Wechsler Intelligence Scale for Children, Fifth Edition (WISC-V) allows for the assessment of the total IQ and consists of 5 main indices (verbal, visuospatial, fluid reasoning, working memory, and processing speed) that are measured from 10 tests. Secondary indices (quantitative, auditory working memory, nonverbal, general ability, and cognitive competence) will also be included [65].

#### Continuous Performance Test

The CPT-3 assesses attention, impulsiveness, and processing speed through a go/no-go interference task where the participant must press the space bar on the keyboard to all letters that appear on a computer screen, except for the letter X (nontarget). The letter presentation interval is 1, 2, and 4 seconds, and the test measures omission errors (unanswered targets), commission errors (answered nontargets), hit reaction time, and response speed variability. The test lasts for 14 minutes [66]. The test positivity cutoff is automatically generated by the program depending on age and sex of the participant.

#### Neuropsychological Evaluation of Executive Functions

The Neuropsychological Evaluation of Executive Functions (ENFEN) is an assessment battery applicable to children between 6 and 12 years old that consists of 4 tests (fluency, paths, rings, and interference) that measure executive functions. The full battery will be used in this study [67].

#### Test for Detecting Dyslexia in Children

For this study, a screening battery consisting of 12 tests known as PROLEXIA (Emooti Neurotech SL) will be used. These tests are applicable from the age of 7 years and are designed to detect symptoms of dyslexia, particularly those related to the phonological component, aiding in differential diagnosis [68].

#### Child Concentration Inventory-Version 2

The Child Concentration Inventory-Version 2 (CCI-2) is a test developed to detect SCT. It is designed to be self-administered by children. It is composed of 16 items, rated on a 4-point Likert scale (0=never, 1=sometimes, 2=often, or 3=always) [69].

### Index Test

The index test (also known as the Bit task) is a go/no-go interference test consisting of 3 parts, preceded by a 4-minute resting-state EEG recording. Each part of the test contains 400 trials, with an interstimulus interval between 450 and 550 milliseconds long. The ratio of go and no-go trials changes across parts, including 25:75 (first part), 50:50 (second part), and 75:25 (third part). If participants make mistakes, a warning will be displayed on the screen reminding them of the instructions. This task will be executed using PsychoPy software (version 2022.1.3; Open Science Tools Ltd).

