**Methods:**

This protocol introduces a single-center, case-control study involving at least 165 participants, aged between 7 and 12 years, that is being conducted at the Puerta de Hierro University Hospital in Madrid, Spain. Participants will be allocated to 3 groups, including ADHD predominantly inattentive, ADHD predominantly combined or hyperactive/impulsive, and a control group, according to the best estimated diagnosis based on clinical interviews and a neuropsychological assessment that includes the Conners Continuous Performance Test. In addition, an EEG recording will be conducted separately, and functional connectivity metrics will be used to characterize brain networks associated with inhibitory control. The index test is expected to match or improve the clinical diagnosis of ADHD in children aged between 7 and 12 years and provide a set of eventual biomarkers that maximize diagnostic performance and provide pathophysiological clues.

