## Methods

### Study Design

This is a noninterventional, case-control, cross-sectional, and assessor-blinded study, which is part of the development of a medical diagnostic test. This manuscript describes the latest version of the study protocol (HUPH-BP-BMCCEEG-CC22 version 4.0, approved on June 7, 2024, as Amendment 4), which was reviewed and approved by the appropriate ethics committee (see below). In order to allow for more complete and detailed reporting, we adhere to 2 acceptable reporting guidelines that match the study design: the Standards for Reporting Diagnostic Accuracy Studies (STARD; Checklist 2) and the SPIRIT (Standard Protocol Items: Recommendations for Interventional Trials) 2025 checklist (Checklist 1) of items to address in a randomized trial protocol, though, *sensu stricto*, our study is not a randomized trial. Following the terminology of the STARD, the EEG and the algorithms used to analyze the EEG data will be regarded as the index test, and the executive control task during which brain connectivity metrics will be pursued will be regarded as the index task. The best estimated diagnosis based on clinical interviews and neuropsychological assessment will be regarded as the reference test. To minimize bias, the PI establishing the reference standard will not perform EEG analyses or access EEG results. Blinding to index test results will be maintained, as no diagnostic or therapeutic decisions will be based on these findings. Consequently, no clinical decision will be influenced by information from the index test. Likewise, the team in charge of EEG processing will not have access to the clinical diagnosis data during data collection for the study. Participants will be categorized into 3 groups, including ADHD predominantly inattentive, ADHD combined or hyperactive/impulsive, and a control group, based on clinical evaluation including the reference CPT-3.

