#### Second Visit

During the second visit, the suspension of medication and abstinence from stimulant substances such as caffeine and xanthines will be confirmed with the participants. Once both have been confirmed, the child’s head circumference will be measured to select the appropriate EEG cap size (S, M, or L). The cap will then be immersed in saline solution for 10 minutes before being placed on the child’s head. The impedance measured in ohms will be assessed at this point.

The EEG recording will begin with a trigger check and a 4-minute eyes-closed resting phase to record brain activity at baseline, followed by the task. The instructions for the task will be introduced, with example trials before full implementation of each part of the task. Throughout the task, breaks will be provided for brief play activities and impedance checks. The EEG session will conclude with the creation of a 3D model of cap placement while the child is wearing the cap.

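### Bit-task warnings after mistakes make the task EEG depend on performance, and the CPT-3 comparison cannot show that EEG rather than the task drives any gain

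*Protocol article*

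**What the plan says.** The Index Test section describes a three-part go/no-go task: "Each part of the test contains 400 trials, with an interstimulus interval between 450 and 550 milliseconds long". The go:no-go ratio moves from 25:75 through 50:50 to 75:25. The same section adds: "If participants make mistakes, a warning will be displayed on the screen reminding them of the instructions". It does not say whether a warning follows each mistake, a run of mistakes, or the end of a block.

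The Second Visit section places the task inside the EEG recording, which starts with a "4-minute eyes-closed resting phase to record brain activity at baseline, followed by the task".

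The label of the index test varies. Study Design says that "the EEG and the algorithms used to analyze the EEG data will be regarded as the index test" and names the task separately as the index task. The Index Test section says: "The index test (also known as the Bit task) is a go/no-go interference test consisting of 3 parts". The last paragraph before the objectives in the Introduction can also be read as giving the label to the Bit task.

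The intended conclusion is about brain networks. Identifying the biomarkers that optimise accuracy is a primary objective. The abstract expects the index test to "provide a set of eventual biomarkers that maximize diagnostic performance and provide pathophysiological clues", and the Discussion presents frequency-domain functional connectivity as the biomarker.

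The one behavioural comparison is a secondary objective: index test against CPT-3, both judged against the investigator's final diagnosis. The abstract's conclusions expect the EEG-based diagnosis to be the more sensitive and specific of the two.

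**The concern.** Because the warning depends on the child's own errors, children do not all see the same sequence of screens while EEG is recorded. Errors are what a go/no-go task is meant to elicit, and ADHD and control children are expected to differ on them. A feature computed from task EEG could then separate the groups partly because it tracks errors or warnings, whatever the state of the attention networks.

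Two conclusions are at stake. One is that the selected features are connectivity biomarkers with pathophysiological meaning. The other is that EEG adds something to a key-press test. The CPT-3 comparison looks like the safeguard for the second, but it changes the task and the measurement method together. A gain over CPT-3 could come from a faster, longer or otherwise more discriminating task, with no contribution from EEG.

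**Working it through.** The article gives no figure of its own on this point, so there is none to reproduce. Trial counts follow from the text; error rates and group separation are assumptions.

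**1. Opportunities for mistakes (Index Test section).** Three parts of 400 trials give 1200 trials. No-go trials: 400 × (0.75 + 0.50 + 0.25) = 300 + 200 + 100 = 600, leaving 600 go trials.

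**2. Possible number of warnings.** If every mistake triggered one (an upper bound, since the rule is not stated), assumed error rates of 5%, 10%, 20% and 30% over 1200 trials give 60, 120, 240 and 360 warnings per child. A group difference in error rate would become a group difference in screen events within the task EEG. The resting segment comes before the task and cannot contain warnings, so the concern is confined to features taken from the task.

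**3. What Bit-task errors alone might achieve.** Let d be the standardised ADHD-control difference in error count (assumed). In an equal-variance binormal model, AUC = Φ(d/√2), and specificity at a fixed true positive fraction (TPF) is Φ(d − z_TPF), with z = 1.282 for 0.90 and 0.842 for 0.80. The Hypotheses section sets a sensitivity threshold of 0.90 with a margin of −0.10, so the bound to exceed is 0.80. The article gives no number for the acceptable false positive fraction.

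| d (assumed) | AUC | Specificity at TPF 0.90 | Specificity at TPF 0.80 |
|---|---|---|---|
| 0.5 | 0.64 | 0.22 | 0.37 |
| 0.8 | 0.71 | 0.32 | 0.48 |
| 1.0 | 0.76 | 0.39 | 0.56 |
| 1.5 | 0.86 | 0.59 | 0.75 |
| 2.0 | 0.92 | 0.76 | 0.88 |

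For d = 1.0: Φ(1/1.414) = Φ(0.707) = 0.76, and Φ(1 − 1.282) = Φ(−0.282) = 0.39.

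These figures describe a classifier that is given the error count directly. They show how strong a behaviour-only benchmark might be. They do not measure how much of the error count leaks into connectivity features.

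**4. Whether CPT-3 can stand in for that benchmark.**

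- Task and pace: CPT-3 presents letters at 1-, 2- and 4-second intervals; the Bit task uses 450 to 550 ms.
- Occasion: the Bit task is done at the second visit, CPT-3 at the third.
- Status: the Statistical Analysis section makes the secondary analyses exploratory, except the first, and the CPT-3 comparison is not the first.
- Independence: Study Design includes CPT-3 in the clinical evaluation that forms the groups. This would tend to favour CPT-3, so it is not a clean measure of what behaviour alone can do. It also says nothing about Bit-task behaviour.

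The comparison can show whether the whole package of Bit task plus EEG beats CPT-3. It cannot apportion a gain between task and EEG.

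**The case against.** A reader might infer that no behaviour-only benchmark is planned. The document does not support that: CPT-3 is scored on omissions, commissions, reaction time and variability, and the comparison with it is a stated secondary objective. What is absent is a benchmark on the Bit task's own responses.

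A reader might also infer that the classifier does read error frequency, or that leaving warning segments unmentioned is a defect. Neither follows. Epoch selection and the handling of error trials are details that an article commonly leaves to the full protocol or the SAP, and nothing says that warning segments enter the connectivity estimates. Leakage is a plausible risk, not a demonstrated fact.

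Nor do the two labels for the index test show that key-press data enter the model. The objectives call the index test EEG-based, and the stated inputs are EEG connectivity metrics. The labels should still be reconciled, because the primary hypothesis concerns this object.

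The strongest objection is that sensitivity and specificity against the reference diagnosis remain interpretable whatever drives the signal, and that the Discussion treats inhibition as central to the disorder. EEG that varies with inhibitory failure may be part of the target. This stands. Connectivity that produces the errors could add nothing beyond them statistically and still be a genuine biomarker, so it would be too strict to allow the term only where EEG improves on behaviour.

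What survives is that the warning is an event added by the task design, and that the planned comparator cannot isolate the contribution of EEG.

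**Conclusion.** The point holds in a limited form. The described design makes the content of the task EEG depend on performance, and the only behavioural comparison planned cannot show that EEG rather than the task accounts for any advantage. This bears on the biomarker interpretation and on any claim of value over task behaviour. It does not invalidate the primary sensitivity and specificity estimates.

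Its size cannot be fixed from the article. Under the binormal model, an assumed separation of 0.5 to 2.0 SD puts a Bit-task error-count benchmark anywhere from an AUC of 0.64 to 0.92. Within that range, error count alone reaches 90% sensitivity with specificity above 0.75 only at about d = 2. It would be wrong to infer that errors alone would probably satisfy the primary criterion: most of the range gives low specificity, and the required specificity is not stated numerically.

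**What to change.** - Use the Study Design definition throughout: the index test is the EEG and its algorithms, without key-press data. Align the Introduction and the Index Test section with it.
- Fit a behaviour-only classifier from the Bit task (omissions, commissions, reaction time and its variability) on the same children and the same folds, and report its paired difference from the EEG model with a confidence interval.
- Add a sensitivity analysis that leaves out warning periods, with the number of epochs equalised across children. Without equalising, error count could return through epoch number. For illustration, with assumed commission rates of 15% and 25% on 600 no-go trials and one trial dropped per warning, losses would be 90/1200 = 7.5% and 150/1200 = 12.5%.
- Claim that EEG adds value over task behaviour only if the paired gain supports it.

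The cost is modest analysis work, fewer epochs in the sensitivity analysis, and possibly a less favourable claim. Enrolment is complete and no new data should be needed. The task must already detect responses in order to issue warnings; that these responses and the warning times are stored is an assumption to confirm.

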### EEG Recording System

We will use the Waveguard net (ANT Neuro) HD-C68 Tyco with Ag rings, 2 HD-C68pin connectors, and 64 semidry electrodes arranged in an equidistant layout, compatible with eego processing software (version 1.9.2 or higher; ANT Neuro). The EEG eego adapter will be used for 6 type A channels, along with the eego amplifier EE-225 (ANT Neuro BV). The reference signal is placed at the 5Z position, while the ground signal is positioned at the 0Z coordinate.

### Participant Recruitment

The study will be conducted in the Department of Psychiatry at the HUPHM. Participants will be recruited from 2 distinct sources. First, cases will be identified by reviewing medical records from the hospital to locate participants with an existing diagnosis of predominantly inattentive, predominantly hyperactive/impulsive, or combined ADHD prior to the commencement of study procedures. Additionally, cases may be prospectively selected from patients routinely seen at the study site who meet the specified selection criteria. These diagnoses will be confirmed through clinical evaluation during the study reference test. Control participants will be recruited from individuals attending Pediatric Services at HUPHM.

Selected candidates will be contacted and invited to participate, with an in-person appointment scheduled to complete the study procedures. ADHD cases will be instructed to temporarily discontinue their medication for the disorder prior to the first visit, with a 24-hour cessation for those using methylphenidate or atomoxetine and 48-hour for those using lisdexamfetamine.

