### Study Visits

#### First Visit

During the first visit, the study’s purpose will be thoroughly explained to participants. Following this, informed consent will be obtained from parents or guardians, and assent will be sought from the child participants. No data will be collected if the participant withdraws consent from the study. The eligibility criteria (Table 1) will be reviewed to confirm participants’ suitability. Additionally, participants will be instructed to abstain from stimulant substances, such as caffeine, xanthines, or medications, 24-48 hours prior to the visit, depending on the type of treatment. If this time frame has not been adhered to, the study evaluation will be rescheduled for the following days.

**Table 1. T1:** Eligibility criteria for participants in the SINCRONIA study.

Participant group	Inclusion		Exclusion	
	Cases (ADHD^a^)	Pediatric controls (non-ADHD)	Cases (ADHD)	Pediatric controls (non-ADHD)
Agreement to participate, with written informed consent obtained from a legal representative together with their own assent	Yes	Yes	No	No
Age (years)	7-12	7-12	<7->13	<7->13
Right-handedness (recruitment of up to 10% of left-handed children is permitted)	Yes	Yes	No	No
Time schedule	ADHD diagnosis within the past 3 years or at the time of the study	Pediatric attendance within the past 3 years or at the time of the study	ADHD diagnosis more than 3 years before the time of the study	Pediatric attendance more than 3 years before the time of the study
Type of ADHD	Predominantly hyperactive/impulsive, or combined presentation, or predominantly inattentive presentation	—^b^	ADHD presentations different from those considered in the inclusion criteria	—
Neuropsychiatric comorbidities	Mild/moderate comorbid conditions (such as anxiety, dyslexia, or SCT^c^) that do not compromise participation	Mild/moderate comorbid conditions (such as anxiety, dyslexia, or SCT) that do not compromise participation	Severe comorbid conditions (such as autism or epilepsy) that may compromise participation	Severe comorbid conditions (such as autism or epilepsy) that may compromise participation
Color blindness or any other condition that may cause instrumental difficulties for sensorineural perception	No	No	Yes	Yes
Severe cognitive or behavioral problems or insufficient capacity to maintain a minimum level of relaxation and rest	No	No	Yes	Yes

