### Risks and Adverse Events

Any adverse events from the EEG recordings, index task, and neuropsychological tests will be recorded according to the clinical guidelines established in the legal framework. Adverse events will be recorded from the first visit to the last. The researcher ([name]) will assess the association between the events and the assessment and report this to the research ethics committee.

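### As written, medicated cases interrupt ADHD medication for the study 24 to 48 hours before the visit at which consent is taken and adverse-event recording starts

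*Protocol article*

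**What the plan says.** The Participant Recruitment section describes the contact that precedes visit 1: "Selected candidates will be contacted and invited to participate, with an in-person appointment scheduled to complete the study procedures". It then states that "ADHD cases will be instructed to temporarily discontinue their medication for the disorder prior to the first visit". The stated length is 24 hours for methylphenidate or atomoxetine and 48 hours for lisdexamfetamine.

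The First Visit section opens with the study's purpose, which "will be thoroughly explained to participants" during that visit. After the explanation, "informed consent will be obtained from parents or guardians", and the child's assent is sought. The Table 1 criteria are reviewed at the same visit to confirm suitability. The section also asks for abstinence from stimulant substances, medications included, for 24 to 48 hours before the visit, and reschedules the evaluation if this was not kept.

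The Second Visit and Third Visit sections each check again that medication has been suspended.

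The Risks and Adverse Events section sets the sources ("Any adverse events from the EEG recordings, index task, and neuropsychological tests will be recorded") and the window ("Adverse events will be recorded from the first visit to the last").

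**The concern.** Two stated sequences do not fit together. A change to a child's treatment made at the study's instruction is timed before the first visit, and the consent that would cover it is timed at the first visit. Read literally, children aged 7 to 12 interrupt treatment for the study before a parent has consented, before they have assented, and before eligibility has been confirmed.

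The adverse-event rule adds a second gap. Its window opens after the first interruption has taken place, and its list of sources leaves interruption out even for the later visits. An event in the day or two before visit 1 has no place in the study record. One before visit 2 or 3 falls within the period but is tied to none of the listed sources.

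What is at stake is participant protection and the completeness of the safety account. Sensitivity, specificity and the hypothesis tests do not depend on it.

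**Working it through.** No power, alpha or event-count calculation bears on this point, and the plan gives no figure to reproduce. The check sets the stated steps in order.

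| Step | Section of the protocol article | Time relative to visit 1 |
|---|---|---|
| Contact, invitation, appointment | Participant Recruitment | before |
| First interruption of ADHD medication | Participant Recruitment | starts 24 h before (methylphenidate, atomoxetine) or 48 h before (lisdexamfetamine) |
| Study explained | First Visit | at visit 1 |
| Consent and assent | First Visit | at visit 1, after the explanation |
| Eligibility confirmed | First Visit | at visit 1 |
| Adverse-event recording opens | Risks and Adverse Events | at visit 1 |
| Suspension checked again | Second Visit, Third Visit | after visit 1 |
| Adverse-event recording closes | Risks and Adverse Events | at the last visit |

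**First interruption against consent.** It starts 24 or 48 hours before the visit at which consent is taken. No section describes an earlier consent step, remote or otherwise. Ethical Considerations says that consent was obtained but not when.

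**First interruption against the recording window.** The window opens at visit 1, so the preceding 24 or 48 hours are not covered.

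**Later interruptions.** Those checked at visits 2 and 3 come after consent and inside the window. The remaining gap is that interruption is not among the named sources.

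**Is the interruption study-driven?** Yes. The evaluation is rescheduled if the time frame was missed, suspension is verified before the EEG and before the CPT-3, and Strengths and Limitations describes the sample as children able to suspend medication. Nothing presents the interruption as routine care.

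**How many children.** The number of medicated cases is not given, so only a ceiling can be computed:

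- Planned: 54 per group × 2 ADHD groups = 108.
- Enrolled: 165 × 2/3 = 110, assuming three equal groups.

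If a share m of cases takes medication, the number affected is 108m to 110m. With m = 0.5, purely as an illustration, that is 54 to 55 children; with m = 1 it is the ceiling. Table 1 admits cases diagnosed at the time of the study, some of whom may be untreated, so m may well be below 1.

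**The case against.** The strongest reply is that the operational order is less settled than the Participant Recruitment sentence suggests. Families are contacted and invited first, and the article does not say what they are told or agree to then. In the First Visit section the abstinence instruction follows the consent sentence, and only the evaluation is rescheduled if the time frame was missed. That would allow consent first and interruption afterwards. The article also condenses a full protocol that is not shown and that may set out an earlier consent step or a wider list of adverse-event sources.

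Part of this stands. The text does not establish that any child actually stopped medication before consent, and practice may have been better than the wording. It does not remove the point. Participant Recruitment places the instruction before the first visit without ambiguity, First Visit places consent at that visit, and the adverse-event section states its own start. These are positive statements, not details left to another document. If later visits were meant, the two sections conflict, and that too needs reconciling.

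A reader might infer more than the documents support:

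- *That all interruption escapes safety capture.* Only the period before visit 1 is outside the window; the interruptions for visits 2 and 3 are inside it.
- *That the design label is contradicted.* Study Design says: "This is a noninterventional, case-control, cross-sectional, and assessor-blinded study". The study assigns no treatment and bases no clinical decision on the index test. Whether a short pause before assessment changes its classification depends on regulations outside the documents.
- *That interruption is the main risk the study imposes.* The article does not rank risks. It can be said only that this is the one change to a child's treatment that it describes.
- *That children stop medication with nothing known of their eligibility.* Cases are found from records of an existing diagnosis or selected as meeting the criteria, and visit 1 confirms this. Screening failures are expected, but their number is not given.
- *That the adverse-event section contradicts the recruitment section.* It does not exclude interruption. It has a window that starts too late to cover the first one and a list that does not name any of them.

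**Conclusion.** The point holds in a limited form. On the article's own wording, the first study-driven interruption precedes consent, assent, confirmation of eligibility and the start of adverse-event recording by 24 or 48 hours, depending on the drug. Later interruptions are consented and within the window but are not a named source of events.

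It concerns medicated cases only: an unknown number, with a ceiling of about 108 to 110. The ceiling rests on the planned group size, or on equal groups among the 165 enrolled, and on every case being treated. The conclusion also rests on there being no earlier consent step, which the article does not mention and the full protocol might.

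This should be corrected for the sake of participant protection and safety reporting. It gives no reason to doubt the diagnostic-accuracy analysis. Because recruitment ended in December 2024, new wording cannot change what happened to enrolled children; for them, what remains is checking and reporting.

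**What to change.** - Reconcile the Participant Recruitment and First Visit sections so that they give one order for consent and the first study-driven interruption. If the full protocol already describes an earlier consent step, the article should say so. No view is taken here on the length or management of the interruption.
- Make the adverse-event window and the list of sources in Risks and Adverse Events cover the interruption periods, both before visit 1 and around visits 2 and 3.
- For children already enrolled, establish from source documents whether the interruption began before consent was signed, and retrieve any events documented in that period. Report both, with the number of cases who were on medication.

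The cost is a wording change plus a check of consent dates and source notes for at most about 110 children. No additional visits are needed, and the accuracy analysis does not change.
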